### Endpoints

The primary endpoint consists of the rate of obstetrical interventions during labor and delivery, defined as caesarean section and instrumental delivery (forceps and vacuum extractor). As secondary endpoints, we include data routinely collected as part of usual antenatal and perinatal care, such as GWG (measured with a scale at each visit), gestational hypertension (defined as systolic blood pressure ≥ 140 mmHg and/or diastolic blood pressure ≥ 90 mmHg after 20 weeks), preeclampsia (defined as gestational hypertension and proteinuria ≥0.30 g/24 h), GDM (diagnosed by a 75 g-oral glucose tolerance test between 24 and 28 weeks according to the guidelines of the International Association of the Diabetes and Pregnancy Study Groups (IADPSG)). Fetal and neonatal collected outcomes, consist of premature birth (defined as birth before 37 weeks), gestational age at birth, birth weight, rate of macrosomia (defined as birth weight > 90th percentile for gestational age), Apgar score, arterial umbilical cord pH, neonatal traumatism, hyperbilirubinemia, respiratory distress syndrome (i.e. needs for oxygen) and transfer in neonatal intensive care unit. Post-natal outcomes are duration of breastfeeding, maternal weight retention and child weight at the postnatal visit (8 ± 2 weeks’ post-partum).

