### Data collection

#### Clinical variables

At inclusion visit between 12 and 22 weeks, demography, medical and family history and current pregnancy health information are collected. Anthropometric variables (weight and height) are measured; blood and urine samples are drawn. No additional follow-up visit is required, as women benefit of the usual care for pregnancy (according to the French guidelines) which consists of 7 prenatal visits and 1 post-natal visit between 6 and 10 weeks after delivery. Information is collected from maternal medical records regarding health during pregnancy including gestational hypertension, preeclampsia and GDM. All women in both groups undergo a 75 g-oral glucose tolerance test (75 g glucose oral load after a fasting period of 10 h minimum) between 24 and 28 weeks. The diagnosis of GDM is made according to the IADPSG criteria (i.e. fasting plasma glucose ≥5.1 mmol/L [0.92 g/L] and/or 1-h glucose ≥10 mmol/L [1.80 g/L] and/or 2-h glucose ≥8.5 mmol/L [1.53 g/L]). The beginning of labor and the delivery mode are collected as well as the occurrence of post-partum hemorrhage. Neonatal and postnatal outcomes include the occurrence of traumatism due to childbirth, Apgar score, umbilical cord pH, admission to neonatal unit and use of phototherapy for hyperbilirubinemia. To address the influence of the intervention on neonatal growth and adiposity, neonatal anthropometric variables (weight, length, adiposity skinfolds) are measured within the first 24 h. At the post-natal visit, maternal demographic data, health since the delivery (post-partum complications such as fever, hemorrhage, thromboembolic events) and duration of breastfeeding are obtained. Maternal anthropometric variables (weight, height) are measured. To address the safety and the impact of the intervention on child health, details regarding the health since birth is also obtained. To address the influence of the intervention on infant adiposity, infant length and weight are measured at birth.

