#### Online assessments

Information on diet habits, eating behaviors, physical activity, motivation stage is collected through self-administered validated questionnaires. The Short Dietary Questionnaire (SDQ) estimates energy nutrient and food intakes based on 14 items of food frequency consumption [32]. The Three Factors Eating Questionnaire (TFEQ) [33] is a food intake-behavior related questionnaire, which contains 21 items and measures three dimensions of eating behavior (cognitive restraint of eating, emotional eating, and uncontrolled eating). The Pregnancy Physical Activity Questionnaire (PPAQ) [34] is a questionnaire of 36 items enable to evaluate the duration, frequency, and intensity of physical activities in pregnant women. The motivation stage is estimated by questioning on the stage of changing [35] in order to follow a healthier diet and practice more physical activity. It contains two 5 stage-questions (see supplemental material). Questionnaires are filled three times during the trial, at the inclusion (between 22 and 25 weeks), at the mid-course of the intervention (between 32 and 35 weeks) and after delivery (up to 10 weeks’ post-partum).

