### Statistics

Statistical analyses will be independently performed by the Biostatistics Department of University of Lille. Data will be analyzed using the SAS software (SAS Institute Inc., Cary, NC, USA) and all statistical tests will be performed with a 2-tailed alpha risk of 0.05. A detailed statistical analysis plan will be written and finalized prior to the database lock. For each exploratory analysis, a statistical analysis plans will be provided before any data analysis. Baseline characteristics will be described for each group. Quantitative variables will be expressed as mean (± standard deviation), median (± interquartile range) and 95% confident interval. Qualitative variables will be expressed as frequencies and percentages. Normality of distribution will be assessed graphically and using the Shapiro-Wilk test. The primary analysis for primary and secondary endpoints will be conducted on the intention-to-treat principle. A secondary per-protocol analysis will be performed.

The primary endpoint (rate of delivery interventions) will be compared between the two groups using the Chi-square test. Absolute and relative risk difference (intervention vs. control) and their 95% confidence intervals will be calculated. For the secondary objectives, binary endpoints will be compared between the two groups using chi-square tests or Fisher’s exact tests when the expected cell frequency will be inferior to 5. Quantitative endpoints will be compared between the two groups using student *t* tests or Mann-Whitney U tests in case of non-normal distribution (except if a log-transformation can be applied to normalize the data). For quantitative endpoints involving repeated measures, a linear mixed model will be used. This model allows to perform an ANOVA for repeated measures taking into account the correlation between the repeated measures. The choice of the covariance in the models will be based on the AIC criteria and normality of residuals will be checked.

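### Single-time quantitative secondary endpoints get an unadjusted test chosen after a normality check, although baseline data and the centre stratum are available and no between-group estimate is named

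*Protocol article*

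**What the plan says.** All of the analysis text is in the Statistics section of the protocol article.

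- Default for endpoints measured once: "Quantitative endpoints will be compared between the two groups using student" t tests.
- Alternative: "Mann-Whitney U tests in case of non-normal distribution (except if a log-transformation can be applied to normalize the data").
- How the choice is made: "Normality of distribution will be assessed graphically and using the Shapiro-Wilk test". No rule covers disagreement between the graph and the test, and the text does not say whether the check is made per arm or on both arms together.
- Endpoints measured repeatedly: "For quantitative endpoints involving repeated measures, a linear mixed model will be used".
- Effect measures: absolute and relative risk differences with confidence intervals are named for the primary binary endpoint. No between-group estimate is named for quantitative endpoints. Descriptively, quantitative variables are to be given as mean, median and a 95% confidence interval.

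Other sections show what is available for adjustment. At the inclusion visit "Anthropometric variables (weight and height) are measured" (Clinical variables). Pre-pregnancy BMI is an eligibility criterion, and inclusion takes place at 12 to 22 weeks (Recruitment and eligibility criteria), so gestational age at inclusion is known. Randomization is stratified by centre (Randomization). The Endpoints section lists "GWG (measured with a scale at each visit"), and under Online assessments "Questionnaires are filled three times during the trial".

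**The concern.** There are two separate weaknesses in the method as written.

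First, the comparison uses none of the baseline information. Maternal weight outcomes are likely to depend on BMI and weight at entry. If GWG is counted from pre-pregnancy weight, part of it has already occurred by randomization and cannot be affected by the programme. An unadjusted test treats that part as noise. Centre was important enough to stratify on but does not appear in the comparison.

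Second, the trial data choose the test. A t test compares means. Mann-Whitney compares distributions by ranks. A t test on logs compares geometric means, as a ratio. Moving between them changes both the hypothesis and the scale. In a trial of this size a formal normality test can trigger the move for departures that do no harm to the t test.

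What is at stake is precision and clear interpretation for secondary endpoints. The Discussion presents control of GWG as the means of reducing maternal and neonatal complications, so a clear estimate in kg is worth having.

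**Working it through.** **Inputs from the article (Sample size):** control rate 50%, intervention rate 40%, two-sided alpha 5%, power 80%, 387 per arm, 774 evaluable, 860 recruited. The article gives no SD, effect, skewness or baseline correlation for any quantitative endpoint, so those below are assumptions.

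**Step 1: reproduce the trial size.** With a mean rate of 0.45,

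n per arm = [1.960 × √(2 × 0.45 × 0.55) + 0.842 × √(0.25 + 0.24)]² / 0.10² ≈ (1.379 + 0.589)² / 0.01 ≈ 387.3.

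Rounded up this is 388, against 387 in the article; power at 387 is 79.97%, and 774 / 0.9 = 860. The size is reproduced and is used here only to fix n.

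**Step 2: how often Shapiro-Wilk rejects at the 5% level.** Simulation, 1,000 runs per row (2,000 for the exact normal). The two columns cover a check per arm and a check on both arms together.

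| Assumed shape | n = 387 | n = 774 |
|---|---|---|
| Exactly normal | 5% | 5% |
| Gamma, skewness 0.1 | 10% | 15% |
| Gamma, skewness 0.2 | 29% | 53% |
| Gamma, skewness 0.3 | 57% | 87% |
| Gamma, skewness 0.4 | 80% | 98% |
| Gamma, skewness 0.5 | 96% | 100% |
| t with 10 df | 56% | 80% |
| Normal, SD 6, rounded to whole units | 22% | 69% |

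**Step 3: does the t test need this protection?** With 387 per arm, the same gamma distribution in both arms and 5,000 runs, type I error was 5.0% at skewness 0.5, 5.2% at 1.0 and 4.9% at 2.0. The simulation error is about √(0.05 × 0.95 / 5,000) = 0.3 percentage points, so all three agree with 5%. Skewness that Shapiro-Wilk nearly always detects leaves the t test intact.

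**Step 4: does the log exception avoid the switch?** Not reliably. GWG and weight retention can be zero or negative, where a log is undefined. Under a normal model with assumed mean and SD of 8 and 6, 9 and 7, or 7 and 6 kg, the share at or below zero is 9%, 10% and 12%. Where a log does work, the result is a ratio and not a difference in kg, g or weeks.

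**Step 5: what adjustment buys.** If r is the correlation between covariate and outcome, the residual variance is multiplied by 1 − r². The equivalent sample size ratio is 1 / (1 − r²). For an assumed standardized difference of 0.2 with 387 per arm, power = Φ(0.2 × √(387/2) / √(1 − r²) − 1.960); unadjusted, this is Φ(2.782 − 1.960) = 79.5%.

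| r (assumed) | Variance factor | Sample size ratio | Power |
|---|---|---|---|
| 0 | 1.00 | 1.00 | 79.5% |
| 0.1 | 0.99 | 1.01 | 79.9% |
| 0.3 | 0.91 | 1.10 | 83.1% |
| 0.5 | 0.75 | 1.33 | 89.5% |
| 0.7 | 0.51 | 1.96 | 97.4% |

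**Step 6: GWG, if analysed as one total from pre-pregnancy weight.** Assume an SD of 5 kg for gain after inclusion and 2, 3 or 4 kg before it. If the two are independent, the variance ratio is (2² + 5²)/5² = 1.16, (3² + 5²)/5² = 1.36 or (4² + 5²)/5² = 1.64. If their correlation is −0.3, the ratio is (E² + 25 − 3E) / (25 × 0.91), with E the SD before inclusion. This gives 23/22.75 = 1.01, 25/22.75 = 1.10 and 29/22.75 = 1.27. The gain is therefore sensitive to an unknown correlation.

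**The case against.** The case on the other side has six parts.

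- **GWG may not fall under this rule.** It is weighed at each visit, so it may go to the linear mixed model, as the questionnaire scores taken three times would. This stands: a reader might infer that GWG will certainly get the unadjusted test, but the article does not say which route it takes. Postpartum weight retention, birth weight and gestational age at birth are single values and remain under the rule.
- **A move of most endpoints to ranks is not shown.** A reader might infer it from Step 2, but the article gives no distributions, and rejection runs from 5% to 100% with the shape. Graphs are also consulted, and a log is tried before ranks. This stands, so the supported wording is that the check can trigger a switch.
- **Means are not lost.** They are to be reported with 95% confidence intervals, so it would be wrong to infer that only a rank p-value will appear. This stands, but a mean per arm is a description and not a named between-arm estimate.
- **The tests are valid and the details belong to the analysis plan.** Validity under randomization stands. A detailed plan is promised before database lock and may add covariates. The point here is different: the article already states a method, and a plan that follows it would inherit the weaknesses.
- **The gain may be small.** Birth weight, gestational age at birth and cord pH have no baseline value of their own. With r of 0.1 to 0.3 the variance falls by only 1 to 9%. This stands.
- **A linear model does not suit everything.** Apgar score is ordinal and bounded. Breastfeeding duration is truncated at the postnatal visit for women still breastfeeding. This stands and limits the fix.

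**Conclusion.** The point holds for continuous secondary endpoints measured once. The stated method leaves collected baseline data and the centre stratum unused. It lets a data-driven check choose the hypothesis and scale, and it names no between-group estimate. At about 387 per arm the check brings no visible benefit: mild skewness of 0.4 to 0.5 is flagged in 80 to 96% of samples, while the t test stays at about 5% up to skewness 2.

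The size of the loss in precision cannot be fixed from the article. Over assumed correlations of 0.1 to 0.7, adjustment removes about 1 to 49% of the variance, with the low end more plausible for endpoints without a baseline value of their own. The Step 6 ratios apply only if GWG is analysed as a single total, and they rest on assumed SDs and correlations.

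No inflation of type I error was found, and the primary chi-square analysis and the sample size are untouched. This is a worthwhile improvement to secondary analyses, not a threat to the trial's main conclusion.

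**What to change.** Make these changes in the statistical analysis plan before database lock:

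1. State whether GWG is analysed as one total or through the mixed model, and from which starting weight it is counted.
2. For continuous endpoints measured once, prespecify a linear model with treatment, centre and the relevant baseline covariates. For GWG and weight retention these are pre-pregnancy BMI, inclusion weight and gestational age at inclusion.
3. Report the adjusted mean difference with its 95% confidence interval and robust standard errors.
4. Drop the choice of test by normality check, and keep Mann-Whitney as a sensitivity analysis.
5. Keep rank-based or other suitable methods for ordinal or truncated endpoints such as Apgar score and breastfeeding duration, and name them in advance.

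This needs no new data and no change to the sample size. The cost is some wording and slightly more analysis work.

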## Discussion

In our Randomized Control Trial, we aim to demonstrate that an e-personalized intervention focused on nutritional counselling and adequate physical activity in pregnant obese women leads to a reduction in delivery procedures (i.e. reduced risk of caesarean section and instrumental deliveries). This program also aims to reduce the risk of maternal and neonatal complications by allowing a better control of GWG. This approach would contribute to maintain or improve the health capital of the mothers and their newborns in the long term. In terms of public health, this action offers, as a primary care, an inexpensive solution that could be proposed to a large number of obese pregnant women. We aim to show that this intervention included in the daily lives of obese pregnant women with reasonable and pragmatic objectives can be associated with a better adherence while a similar effectiveness is maintained in comparison with more complex programs. Our most important challenge is to create for participants a mind-set that motivates them to change their lifestyle, in other words to help them understand how eating healthy food and being active in pregnancy is important for their health and the health of their offspring. This program will also give the tools and supports which they need to reach their objectives. ePPOP-ID will give them self-confidence and self-esteem necessary to instill positive self-images.

Pregnancy is a very privileged time to have or to keep good health habits and to diffuse them within the family to promote more sustainable lifestyle improvements. Time of pregnancy seems to be a privileged moment during which future parents pay more attention to establish lifestyle changes. This project will offer to the health institutions and to stakeholders’ actions to be disseminated widely in pregnant obese patients and their caregivers. The broader goal is to contribute to the development of therapeutic and preventive tools to limit the dramatic consequences of obesity in pregnancy and to fight against the growing obesity epidemic by acting at a key moment of the women life.

## Data Availability

Not applicable.

## Abbreviations

BMI: Body Mass Index
GDM: Gestational Diabetes Mellitus
GWG: Gestational weight gain
IOM: Institute of medicine
LGA: Large for Gestational Age
PPAQ: Pregnancy Physical Activity Questionnaire
SGA: Small-for-gestational-age
TFEQ: Three Factors Eating Questionnaire
